#### Secondary outcomes

The following secondary outcomes will be assessed:
Gestation at booking;Booking before 25 weeks;Measures of size: crown to heel length, head circumference;Measures of stage: gestational age at delivery, weight-for-dates (standardised; SGA babies are those weighted less than the 5th centile weight, or LGA weighted more than the 90th centile weight), term at birth (preterm, babies are born at less than 37 weeks gestation; term babies are those born between 37 and 42 weeks gestation and post-term babies are born after 42 weeks gestation);Birth outcomes: mode of delivery, stillbirths, neonatal deaths, 5 min Apgar score. Although there is some debate concerning the robustness of the Apgar score as an outcome, it is in common use and we will therefore present results for this outcome within the context of the wide debate on the subject.

Due in part to the introduction of smoking ban in Scotland in 2006, an additional outcome of interest is maternal smoking. Maternal smoking is collected at booking and during pregnancy. The health advice given when receiving the HiP grant might have an impact on smoking rates during pregnancy over and above that of the smoke-free legislation. We will analyse the temporal change in smoking rate by socioeconomic class and its effect on outcomes.

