### Sample size

The data are clustered in small areas, 6505 data zones. The sample size calculation takes this clustering into account. Assuming an average of 56 000 singleton live births per year, and allowing for the clustering within the 6505 data zones in Scotland (average population 780/data zone) with an estimated intraclass correlation coefficient of 0.05, we have power of 0.90 to detect an effect of 7 g change in birth weight at a 95% significance level. This is not to say that 7 g is a clinically important threshold; rather, it is indicative of the power of the study. The large national data set available to us will allow for subgroup analysis. In the 20% most deprived areas, we will have power of 0.80 to detect an effect of 13 g; among the 26% of single mothers, we will have power of 0.80 to detect an effect of 11 g. To put these small effects into context, 50 g is the estimated mean birth weight reduction reported in the meta-analysis of the effect of interventions in pregnancy on maternal and obstetric outcomes.^27^

We anticipate item non-response for some outcomes and explanatory variables. Our primary outcome measure, birth weight, has a completion rate of 99.9%. There is high completion rate (<1.5% missing) for all obstetric variables,^46^ with the exception of crown to heel length (15% missing) and head circumference (12% missing). The item non-response ranges from 8% for maternal smoking to 20% for marital status. We will use multiple imputation to account for missing data and all analyses will compare the results of analyses of complete cases and multiple imputation.^63^ Imputed models will be constructed such that they contain as many relevant predictor variables as possible. The more variables that are used the greater the amount of information available on which estimations are made. We will use all (or as many as possible) obstetric and maternal variables in an imputation model to predict the missing values. It is difficult to identify in advance the number of multiple imputed data sets we will need to construct but it is likely to be between 5 and 10. We will then analyse these data sets identically and combine the results to get the estimates and SEs for the multiple imputed data. These results will be compared with the complete case analysis results.

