The simplest model for the intervention effect will include a dummy variable ‘intervention’ covering the period from the introduction to the withdrawal of HiP grants, with adjustment for relevant factors such as marital status. (More complex models of the effect of the intervention will include an interaction of the intervention with the temporal trend.) Before carrying out specific subgroup analysis, we will identify differential effects by fitting interaction terms. An assessment as to whether there is a differential effect of the intervention for single women, for example, will involve a test of the significance of the intervention between marital status and the intervention effect. If the interaction is significant this will aid our understanding of the generalisability to other populations, including the rest of the UK. Subgroup analyses will be conducted for those groups seen as having the greatest potential to benefit from the payments such as those living in the most deprived areas, those in the lowest social classes, lone mothers, primiparous women, teen mothers, mothers from ethnic minorities and selected combinations of these groups. For each group we will replicate the main analysis. This reduction in sample size for subgroup analyses will result in fewer women/births being available but the same number of areas (data zones) will be analysed (apart from analyses restricted to those living in the most deprived areas).

An increase in birth weight, although desirable at a population level, may not be a beneficial outcome if the baby were already at risk of being LGA. Separate subgroup analyses will therefore be conducted for women seen to be at high risk of delivering a LGA baby (women with diabetes) and for the remainder of the population. Given that some subgroups may contain small numbers, and bearing in mind the potential importance of the intervention, we will report the results of all subgroup analyses and not just those that reach statistical significance to avoid false negatives. The above process will involve conducting many tests, which will not be independent of each other. Rather than adjusting CIs or p values to account for this we will present the results of all analyses and caution the user regarding the interpretation of the results. Indeed, some statisticians recommend never correcting for multiple comparisons while analysing data.^65^

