^66^ According to Rothman,^65^ reducing the type I error for null associations increases the type II error for those associations that are not null. He recommends a policy of not making adjustments for multiple comparisons because it will lead to fewer errors of interpretation when the data under evaluation are not random numbers but actual observations on nature.

The HiP grant was introduced and withdrawn at the same time as other interventions that may have an impact on birth weight. Healthy Start is a means tested voucher scheme for pregnant women. If they are in receipt of certain benefits or under 18 years old, then they are eligible for free vitamins and vouchers to be spent on fruits and vegetables. This scheme replaced the means tested parts of the Welfare Food Scheme in the UK (including Scotland in 2006) and is still currently in place. During this period, there were policy changes in the optimal timing of first booking appointments due to changes in blood tests offered to pregnant women in the Pregnancy Screening Programme. These changes were first discussed in 2008 and had to be implemented by all Health Boards by March 2011.^67^
^68^ Early booking is a HEAT target of the Scottish Government (Health improvement for the people of Scotland, Efficiency and governance improvements, Access to services, Treatment appropriate to individuals H11.1).^69^ At least 80% of pregnant women in each SIMD quintile will have booked for antenatal care by the 12th week of gestation by March 2015.

A further piece of legislation that may affect birth weight is the introduction of the smoking ban in public places in Scotland in March 2006. Mackay *et al*^70^ reported a reduction in the prevalence of current smoking among women who conceived after the introduction of the legislation prohibiting smoking. They also reported a reduction in small and very SGA, as well as in absolute LBW after the legislation. We will carry out a further analysis restricting the preintervention HiP grant period to April 2006 to March 2009.

It is possible that harm may have occurred due to the cash transfer. The £190 was given to pregnant women with no restriction as to how it should be spent, and we do not know how the money was used. We are examining how the intervention group differed; birth weight could have reduced or increased. We will carry out two-sided hypothesis tests to ensure that we are able to detect any such potential harmful effect.

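### The test for differential effects names no subgroup-specific time trend, so a difference in birth-weight trend between subgroups would leak into the subgroup-by-intervention term

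*Protocol article*

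**What the plan says.** Under Data analysis plan, Statistical analysis, the simplest model has one dummy variable for the grant period plus adjustment. A more complex model adds an interaction of the intervention with the temporal trend. On subgroups the section says: "Before carrying out specific subgroup analysis, we will identify differential effects by fitting interaction terms". For single women, as the example, this "will involve a test of the significance of the intervention between marital status and the intervention effect". Subgroup analyses then follow: "For each group we will replicate the main analysis". All of them are to be reported, whether or not they are significant.

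The same section adjusts all analyses for temporal trend and season without saying whether either may vary by subgroup. Table 2 lists date of birth as a single covariate line. The only trend interaction named anywhere is intervention by trend.

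The Introduction gives differential impact as the first specific research question. The second asks how cost-effectiveness varies across subgroups found to have differential outcomes.

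**The concern.** Subgroup by intervention is the only test of a difference between groups that the article describes. Suppose the model holds a single trend, and birth weight in one subgroup drifts relative to the rest for reasons unrelated to the grant. Part of that drift is then attributed to the grant. The sign follows the drift, so the result may be a spurious differential effect or a real one that is masked.

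The article gives some reason not to rule out such drift. Healthy Start reached Scotland in 2006 and is aimed at women on certain benefits or under 18, who overlap with the deprived and teenage subgroups. It is not a listed covariate, and Table 2 lists maternal nutrition and education as unmeasured.

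The models fitted within each subgroup estimate their own trend. The test and the subgroup results therefore rest on different assumptions, and the article does not say which prevails if they disagree. At stake is the reading of who benefited. That reading feeds the cost-effectiveness comparison and, under Economic analysis and Implications, possible policy recommendations that differ by socioeconomic group.

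**Working it through.** **The plan's own power figure.** Under Sample size: "we have power of 0.90 to detect an effect of 7 g change in birth weight at a 95% significance level", "Assuming an average of 56 000 singleton live births per year" and "with an estimated intraclass correlation coefficient of 0.05". Tests are two-sided. Study population gives 63 months before, 25 during and 32 after the grant. At 56 000/12 = 4 667 births a month, that is about 116 667 exposed and 443 333 unexposed births.

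- SE needed: 7/(1.960 + 1.282) = 2.16 g.
- √(1/116 667 + 1/443 333) = 0.00329.
- Implied SD with no design effect: 2.16/0.00329 = 656 g.
- With design effect 1 + 7.6 × 0.05 = 1.38 (8.6 births per data zone per year): 559 g.
- With design effect 1 + 85 × 0.05 = 5.25 (86 births per zone over ten years): 286 g.

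The article gives no SD, so the 0.90 cannot be confirmed. Below, an SD of 550 g is assumed (range 450–600 g). The bias figures do not depend on it.

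**Bias factor.** Number the months 1 to 120.

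- Grant months 64–88: mean 76.0.
- Other months: (7 260 − 25 × 76)/95 = 5 360/95 = 56.4.
- Gap: 19.58 months = 1.63 years.

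With a shared trend and a constant subgroup share, the interaction is a difference of differences. The shared trend cancels and a linear slope difference d remains multiplied by the gap, so bias = 1.63d. Adding a common intervention-by-trend term leaves this factor unchanged.

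**Size over an assumed range of d.** The SE of the interaction is SD × 0.00329 × √(1/p + 1/(1 − p)), where p is the subgroup share. At SD 550 g it is 4.13 g for p = 0.26 (single mothers) and 4.52 g for p = 0.20 (most deprived areas). The last two columns give the two-sided 5% rejection rate when there is no true interaction.

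| d (g/year) | Bias (g) | p = 0.26 | p = 0.20 |
|---|---|---|---|
| 1 | 1.6 | 7% | 7% |
| 2 | 3.3 | 12% | 11% |
| 3 | 4.9 | 22% | 19% |
| 5 | 8.2 | 51% | 44% |

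At d = 5 and p = 0.26 the rate runs from 44% (SD 600 g) to 68% (SD 450 g). These rates assume independent births; clustering and serial correlation are not modelled.

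For scale, the article's detectable within-subgroup effects are 11 g and 13 g. A spurious interaction of that size needs d = 11/1.63 = 6.7 or 13/1.63 = 8.0 g/year.

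**With subgroup by trend added.** The bias is zero for any linear d. The cost in SE follows from the correlation between the grant indicator and time:

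- R² = (25/120)(95/120) × 19.58²/[(120² − 1)/12] = 0.0527.
- SE ratio = 1/√(1 − 0.0527) = 1.027.
- The SE goes from 4.13 to 4.24 g (p = 0.26) and from 4.52 to 4.65 g (p = 0.20).

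**Effect of the design on the size of the problem.**

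- With no post-grant period the factor would be 76 − 32 = 44 months, or 3.67. The on–off design has already cut it to 1.63.
- With the baseline starting in April 2006 (month 28), the other 68 months average 73.3 and the factor falls to 2.74/12 = 0.23. At d = 5 that is 1.1 g.

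**The case against.** The common trend is inferred from silence. The article never says that trend is shared across subgroups, it speaks of interaction terms in the plural, and a journal article may leave exact model terms to a fuller plan. Smoking, maternal age, weight at booking, social class and area deprivation are already adjusted for, so only a slope difference that survives this can do harm. Each subgroup is refitted with its own trend, which carries no bias from a linear trend difference, and every subgroup result is reported. A further analysis starts the baseline in April 2006, which removes most of the bias.

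Much of this stands as a limit on size. It does not repair the test. The article does spell out the term to be tested and does name a trend interaction, and subgroup by trend is not it. A stratified fit estimates an effect within a group and does not test a difference between groups. The April 2006 analysis is aimed at the smoking ban and is not tied to the interaction tests.

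A reader might go further and infer that subgroups with different trends will appear to have responded to the grant. The documents do not support that, because they give no size for any trend difference. Nor do they say that such differences are expected. On smoking, the article says only: "We will analyse the temporal change in smoking rate by socioeconomic class and its effect on outcomes". That is a plan to look and states no expectation. The cited disparities that were maintained or grew over time are urban–rural ones in Alabama, and they do not concern the subgroups tested here. The choice not to adjust for multiple testing is separate, disclosed and argued.

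**Conclusion.** The point holds in a limited form. Followed as written, the differential-effect test lacks a subgroup-specific trend and is biased by 1.63 g for each 1 g/year of linear trend difference left after covariate adjustment. At 1–2 g/year the harm is modest: 1.6–3.3 g, and a false-positive rate of about 7–12% at SD 550 g. It becomes serious only at several g/year, and nothing in the article shows whether differences of that size exist. The factor assumes a shared linear trend, a constant subgroup share and even monthly births. The rejection rates also rest on the assumed SD and on independence of births. The practical risk is that the only between-group test can disagree with the subgroup estimates beside it. This is a cheap improvement to the specification and does not invalidate the design.

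**What to change.** State that every differential-effect test includes subgroup by time trend alongside subgroup by intervention, with trend in the same form as in the main model, so that the test matches the subgroup fits already planned. If the main model allows a non-linear trend, the subgroup trend should be equally flexible, because the linear term removes only linear differences.

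The cost is one sentence and a confidence interval for the interaction about 3% wider. That figure is for a linear trend and independent births. A subgroup-by-season term, and making the interaction the primary subgroup result, are optional and not needed for this repair.

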^16–18^ In a study of social class inequalities in perinatal outcomes in Scotland, Fairley and Leyland^19^ reported a percentage of 5.8% LBW in unskilled social class (V) compared with 2.9% in professional social class (I) between 1995 and 2000. The systematic review and meta-analyses of social inequality and infant health in the UK performed by Weightman *et al*^20^ found that the OR for LBW was 1.79 (95% CI 1.43 to 2.24) in the lowest compared with the highest social class. This effect may vary with maternal factors such as age and smoking status. Smoking during pregnancy reduces birth weight by 162–377 g, depending on daily consumption (larger reduction for heavy smokers) and the trimester in which exposure occurs (larger reduction during the last trimester).^18^
^21^
^22^

The association between maternal nutrition and birth outcome is complex and is influenced by many biological, socioeconomic and demographic factors, which vary widely in different populations.^23^
^24^ However, it has been reported that favourable prenatal nutrition associated with adequate prenatal care can have a positive impact on birth outcomes and morbidity in adult life.^25^
^26^ Indeed, the developmental model of the origins of chronic disease proposes the causal influence of undernutrition *in utero* on coronary heart disease and stroke in adult life.^7–9^ An improvement in fetal nutrition may therefore have far reaching consequences in terms of the prevention of disease. A review of maternal nutrition and birth outcomes identified improving maternal nutrition as being beneficial to the prevention of adverse birth outcomes in lower social class groups.^24^

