In the UK, the Health in Pregnancy (HiP) grant was introduced for women reaching the 25th week of pregnancy with a due date on/or after 6 April 2009. It was subsequently withdrawn for women reaching the 25th week of pregnancy on/or after 1 January 2011. The HiP grant was a universal conditional cash transfer of £190 for women reaching 25 weeks of pregnancy if they had sought health advice from a doctor or midwife. It was designed to provide additional financial support, in the last months of pregnancy, towards a healthy lifestyle including diet, and it was suggested that the link to the requirement for pregnant women to seek health advice from a professional may provide a greater incentive for expectant mothers to seek the recommended health advice at the appropriate time. The grant was paid and administered by Her Majesty's Revenue and Customs (HMRC) on receipt of a claim form partly completed by the midwife or doctor. Advice was offered as normal by doctors and midwives. Payment was made directly into a bank account with a telephone helpline available to provide support through the claims process including options for payment in the event of difficulties opening a bank account. Take-up of the HiP grant was similar to that of child benefit (98–99%, personal communication, HMRC).

The current study focuses on the evaluation of the effectiveness and cost-effectiveness of the HiP grant. As a primary outcome, we will consider the difference in birth weight for babies born to those mothers who were eligible for the HiP grant with babies born before the HiP grant was introduced or after it was withdrawn. Specific questions the research project will address are:
Were there differential impacts of the intervention for particular subgroups defined by socioeconomic (defined in terms of both area deprivation and individual occupational social class), demographic (marital status, age, maternal height), or obstetric (parity, previous caesarean section) factors or for selected combination of these groups?Was the HiP grant cost-effective? How did cost-effectiveness vary across important subgroups identified as having differential outcomes?

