### Data analysis plan

#### Statistical analysis

Descriptive statistics of all variables will be presented as mean, SD, minimum, median and maximum for continuous variables and as proportions when the variables are categorical.

The main statistical design we will use is interrupted time series.^64^ Segmented regression analysis will allow an estimation of the size of the effect of the HiP grant at different time points, as well as changes in the trend of the effect over time after its implementation.

Outcomes will be measured on individual births, which are nested within mothers, with mothers themselves clustered within data zones and Health Boards. Multilevel univariable and multivariable models will be used to determine whether the outcomes changed during the period in which the HiP grants were in effect. Multilevel linear regression will be used when the outcome is continuous and multilevel binomial logistic regression when the outcome is dichotomous. Multilevel multinomial logistic regression will be used for the multicategory outcomes mode of delivery and 5 min Apgar score.

All analyses will be adjusted for temporal trends and seasonal variations in outcomes in addition to maternal age, sex of child, parity, marital status, height, weight at booking, diabetes, smoking status, gestation at booking, maternal diabetes, social class, maternal smoking and area deprivation.

The effect of HiP grant on birth weight might have a carryover effect after the withdrawal of the grant. In other words, postintervention the slope in birth weight might not fall back to the same rate as preintervention. This could be due to women who have gave birth during the intervention subsequently having a birth postintervention but still heeding the health advice given during their first pregnancy. We will carry out an additional analysis only on primiparous women to avoid such contamination.

We will analyse preterm births stratified by mode of delivery and stratified according to whether the birth was induced or spontaneous.

We will repeat the main analyses including (ie, adjusting for the effect of) ethnicity along with other covariates and compare the results with analyses excluding ethnicity to gauge the impact of this on our results. We note that the quality of this variable (including the completeness of recording) is poorer than for other variables and that only 1–2% of mothers delivering in Scotland are from minority ethnic backgrounds.

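### For the binary and categorical secondary outcomes, differential effects are identified on the odds-ratio scale, but the subgroup cost-effectiveness question they feed depends on absolute effects

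*Protocol article*

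**What the plan says.** The Statistical analysis section sets the model by outcome type: "Multilevel linear regression will be used when the outcome is continuous and multilevel binomial logistic regression when the outcome is dichotomous". Table 2 of the protocol article assigns binomial logistic models to booking before 25 weeks, weight-for-dates, stillbirth, neonatal death and maternal smoking. It assigns multinomial logistic models to term at birth, mode of delivery and 5 min Apgar score. Birth weight, the primary outcome, has a linear model.

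On heterogeneity the same section says: "Before carrying out specific subgroup analysis, we will identify differential effects by fitting interaction terms". The criterion is a significance test; for single women the assessment "will involve a test of the significance of the intervention between marital status and the intervention effect". The section continues: "Subgroup analyses will be conducted for those groups seen as having the greatest potential to benefit from the payments", and "For each group we will replicate the main analysis". It commits to reporting every subgroup result, significant or not.

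The Introduction poses the economic question this way: "How did cost-effectiveness vary across important subgroups identified as having differential outcomes". The Economic analysis section sets the cost of the grant (£190 plus administration) against birth weight changes and secondary end points, with stillbirth as its example. It compares cost-effectiveness between the socioeconomic groups that the main analysis identifies, and it foresees policy recommendations that differ by group. The article names no risk difference or other absolute measure of differential effect for the binary outcomes.

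**The concern.** An interaction term in a binomial logistic model is zero when the odds ratio is the same in both groups. In a multinomial model the same holds for the odds of each category against the reference category. The research questions concern differential impact and value for money by socioeconomic group, and these turn on events avoided per woman paid. If baseline risks differ, a common odds ratio is itself a difference in absolute benefit, and the planned test cannot see it. Fitting the same logistic model within each subgroup does not help, since it again returns an odds ratio.

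At stake is the interpretation of the secondary outcomes in the choice between universal and targeted payment, which the article raises in its Introduction and returns to under Implications. A null logistic interaction could be taken to mean that the grant did equally much for all groups when it did more, in absolute terms, for the group at higher risk.

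**Working it through.** The plan states no figure for any binary outcome or for any interaction, so there is nothing to reproduce. The stated power for a 7 g change concerns the continuous primary outcome and has no bearing here.

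**Inputs**
- Baseline risks of low birth weight: 5.8% (social class V) and 2.9% (class I), from the Introduction, for 1995 to 2000. These are the only group-specific risks of a binary outcome in the article.
- Social-class odds ratio for low birth weight: 1.79, from the review cited in the Introduction.
- Common odds ratio for the grant: not given. Assumed 0.90, with a range of 0.95 to 0.50.

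**Formula.** With baseline risk p and odds ratio OR, the risk under the grant is p' = OR·p / (1 − p + OR·p), and the absolute benefit is p − p'.

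**Common OR of 0.90**
- Class V: p' = 0.0522 / 0.9942 = 0.05250; benefit 0.00550, or 5.50 per 1000.
- Class I: p' = 0.0261 / 0.9971 = 0.02618; benefit 0.00282, or 2.82 per 1000.
- Ratio of benefits 1.95. The logistic interaction is exactly zero.
- On the £190 alone, without administration costs, the cost per event avoided is 190 / 0.005495 ≈ £34,600 and 190 / 0.002824 ≈ £67,300.

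**Sensitivity to the assumed OR (5.8% v 2.9%)**

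| OR | Avoided per 1000, class V | Avoided per 1000, class I | Ratio |
|---|---|---|---|
| 0.95 | 2.74 | 1.41 | 1.94 |
| 0.90 | 5.50 | 2.82 | 1.95 |
| 0.80 | 11.06 | 5.67 | 1.95 |
| 0.50 | 28.13 | 14.29 | 1.97 |

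**Sensitivity to the baseline contrast (OR 0.90)**
- 2.9% with the review's odds ratio of 1.79 gives a comparison risk of 5.07%; ratio of benefits 1.71.
- Hypothetical 2:1 risks: 0.5% v 0.25% gives about 2.0; 10% v 5% gives 1.90; 40% v 20% gives 0.0250 / 0.0163 = 1.53.

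**The reverse case.** An equal benefit of 3 per 1000 in both classes corresponds to odds ratios of 0.945 (class V) and 0.894 (class I), a ratio of 1.06. The odds-ratio scale then shows the larger effect in the lower-risk class although the absolute benefits are the same.

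**The case against.** A reader might infer more than the article says, in four ways.

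- *Groups with equal odds ratios will be declared alike.* No such rule appears. The article says only that a significant interaction would help in understanding generalisability. It analyses the named disadvantaged groups without making this conditional on the interaction, and it reports all the results.
- *Higher-risk groups will drop out of the economic comparison.* The Introduction speaks of subgroups identified as differing, but it does not restrict the comparison to them or say that the logistic test identifies them. A cost-per-QALY model needs absolute effects, and the analysts may well convert odds ratios using each group's baseline risk.
- *The absolute benefit is twice as large in the disadvantaged group.* That factor rests on low-birth-weight risks. The Study variables section mentions low birth weight as a project outcome, but it is absent from the Secondary outcomes list and from Table 2. The article gives no subgroup risks for the outcomes that are listed there with logistic models, and the factor falls as outcomes become more common.
- *The main result is affected.* It is not. The birth weight interaction is already additive, and birth weight comes first among the economic benefits.

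It can also be said that logistic interactions are standard, and that a condensed article leaves post-estimation detail to a fuller plan. All of this stands as a limit on the point. What remains is that the article states a method for identifying differential effects, that this method works on the odds-ratio scale, and that the economic question it feeds needs the absolute scale. Reporting every subgroup does not close that gap while each subgroup result is an odds ratio.

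**Conclusion.** The point holds for the binary and categorical secondary outcomes only. The stated test of differential effect assesses odds ratios, whereas subgroup cost-effectiveness depends on risk differences. With a common odds ratio, the hidden difference in absolute benefit is about 1.95-fold at 5.8% against 2.9%, about 1.7-fold with the review's odds ratio, and about 1.5-fold for a common outcome at 40% against 20%. These are illustrations: the grant odds ratio is assumed, and the 40% and 20% risks are hypothetical. This is a mismatch of scale that is cheap to mend. It is not an error in the primary analysis, and it does not show that any group will be left out.

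**What to change.** For each binary and categorical secondary outcome:

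1. Report the grant effect in every pre-listed subgroup as a standardised risk difference with a confidence interval. Obtain it from the fitted model as the mean predicted risk with the grant term on and off, averaging over covariates and random effects.
2. Assess effect modification on the absolute scale, as the contrast of these risk differences between groups with its confidence interval, beside the odds-ratio interaction.
3. In the economic analysis, compare all pre-listed socioeconomic groups using their absolute effects, whether or not the logistic interaction is significant.

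No new data or models are needed. The cost is a little post-estimation work and the need to present and explain two scales, which may at times point in different directions.
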